# Identifying the Characteristics of Responders and Nonresponders in a Behavioral Intervention to Increase Physical Activity Among Patients With Moderate to Severe Asthma: Protocol for a Prospective Pragmatic Study

**DOI:** 10.2196/49032

**Published:** 2023-08-31

**Keywords:** asthma, behavioral intervention, physical activity, responders

## Abstract

**Background:**

Previous research has suggested that most adults improve their asthma control after a short-term behavioral intervention program to increase physical activity in daily life (PADL). However, the characteristics of individuals who respond and do not respond to this intervention and the medium-term response remain unknown.

**Objective:**

This study aims to (1) identify the characteristics of adult responders and nonresponders with asthma to a behavioral intervention to increase physical activity and (2) evaluate the functional and clinical benefits in the medium term.

**Methods:**

This prospective pragmatic study will include adults with moderate to severe asthma who enroll in a behavioral intervention. All individuals will receive an educational program and an 8-week intervention to increase PADL (1 time/wk; up to 90 min/session). The educational program will be conducted in a class setting through group discussions and video presentations. Behavioral interventions will be based on the transtheoretical model using counseling, incentives, and individual feedback aiming to increase participation in physical activity. Motivational interviewing and guidelines for overcoming barriers will be used to stimulate individuals to reach their goals. Pre- and postintervention assessments will include the following: PADL (triaxial accelerometry), body composition (octopolar bioimpedance), barriers to PADL (questionnaire), clinical asthma control (Asthma Control Questionnaire), quality of life (Asthma Quality of Life Questionnaire), anxiety and depression levels (Hospital Anxiety and Depression Scale), and exacerbations. “Responders” to the intervention will be defined as those who demonstrate an increase in the number of daily steps (≥2500).

**Results:**

In December 2021, the clinical trial registration was approved. Recruitment and data collection for the trial is ongoing, and the results of this study are likely to be published in late 2024.

**Conclusions:**

The intervention will likely promote different effects according to the clinical characteristics of the individuals, including asthma control, age, anxiety and depression levels, obesity, and several comorbidities. Identifying individuals who respond or do not respond to behavioral interventions to increase PADL will help clinicians prescribe specific interventions to adults with asthma.

**Trial Registration:**

ClinicalTrials.gov NCT05159076; https://clinicaltrials.gov/ct2/show/NCT05159076

**International Registered Report Identifier (IRRID):**

DERR1-10.2196/49032

## Introduction

According to the Global Initiative for Asthma (GINA), asthma is a heterogeneous disease characterized by chronic airway inflammation [1]. Asthma is defined by the history of respiratory symptoms, such as shortness of breath, wheezing, chest tightness, and cough, which can vary over time and in intensity, together with variable expiratory airflow limitation [1]. Asthma is a global health problem that affects all age groups. For example, in 2019, about 262 million people were diagnosed with asthma, and 461,000 died from this disease [2]. Moreover, its prevalence is increasing, affecting up to 18% of the population in some countries [1].

Several treatments, both pharmacological and nonpharmacological, are involved in the control of asthma. A supervised, structured exercise program is a nonpharmacological treatment known to improve asthma control [3]. However, despite the proven benefits of exercise, several barriers, such as the lack of space, limited access to pulmonary rehabilitation programs, and decreased motivation to remain physically active after the completion of such programs [4], make interventions to increase physical activity in daily life (PADL) an attractive and viable option [5].

Despite the known benefits of being physically active that have already been shown in this population, individuals with asthma are less physically active than control populations [6]. For instance, a previous study demonstrated that physical inactivity and a sedentary lifestyle are the only extrapulmonary factors associated with asthma exacerbation [7]. In addition, higher levels of physical activity positively impacted the clinical outcomes in this group [6]. Consequently, it is important to develop strategies to modify behavior to increase physical activity and reduce sedentary activities in this population.

The World Health Organization (WHO) recommends that adults perform 150 to 300 minutes of moderate-intensity aerobic physical activity weekly to achieve certain health benefits [8]. In addition, international guidelines [9] and GINA [1] classify, with A-level evidence, people with asthma who engage in regular physical activity to reduce cardiovascular risk and improve their quality of life [1]. A previous study found that a behavioral intervention to increase PADL improves clinical asthma control, sleep quality, and anxiety symptoms in adults with moderate to severe asthma [5]. However, 17% of the individuals did not improve their physical activity level, and 25% did not improve their clinical control after the intervention. Individuals with other chronic respiratory [10], cardiac [11], musculoskeletal [12], and neurological diseases [13] have also been classified as better or worse responders to specific interventions.

Thus, despite the benefits obtained by behavioral intervention aimed at increasing PADL in adults with asthma [5], it is necessary to know the characteristics of responders and nonresponders to guide the management in a more personalized approach. Moreover, the effects of this intervention were only assessed in the short term (immediately after the intervention), and the medium-term effects remained unknown. We hypothesize that the intervention might cause different effects according to the clinical characteristics of the individuals, including asthma control, age, anxiety and depression levels, obesity, and several comorbidities. Therefore, the main objective this prospective cohort study will be to identify the characteristics of adult responders and nonresponders with moderate to severe asthma to a behavioral intervention to increase PADL and evaluate the functional and clinical responses in the short and medium terms.

## Methods

### Study Design

This prospective cohort study will be conducted at a university hospital that provides specialized asthma treatment. The study protocol was developed following the SPIRIT (Standard Protocol Items: Recommendations for Interventional Trials) checklist guidelines [14], and the trial was registered at ClinicalTrials.gov (NCT05159076). The study design is illustrated in Figure 1. Individuals with asthma will be enrolled in the trial after a routine medical consultation. Baseline lung function will be checked from the medical records. Eligible participants will undergo an 8-week behavioral intervention protocol to increase PADL and reduce sedentary behavior. First, all included individuals will receive an educational program, followed by an intervention aimed at increasing physical activity. All individuals will be assessed before and after the 8-week intervention and then 16 weeks later. The outcomes assessed will include anthropometric variables, clinical asthma control, health-related quality of life, physical activity levels, anxiety and depression symptoms, exacerbations, body composition, barriers to performing PADL, and physical activity behavioral stages (Figure 1).

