#### Participant Timeline

The schedule of enrollment, interventions, and assessments is outlined in Table 2. The recruitment of the study participants began in May 2022.

**Table 2 table2:** Content for the schedule of enrollment, interventions, and assessments.

		Time point				
		Enrollment	Allocation	Postallocation		
		–*t*_1_	0	Baseline	8 Weeks	16-Week follow-up

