### Statistical Analysis Planning

Individuals will be stratified as “responders” and “nonresponders” based on an increase of ≥2500 steps [45]. The Kolmogorov-Smirnov test will be used to assess data normality. Cluster analysis will be used to characterize the groups according to individual characteristics. Cluster analysis will be carried out in 2 stages: hierarchical analysis using the Ward method to determine the number of clusters and k-means analysis to group the clusters [46]. Comparisons of clinical, anthropometric, and psychosocial data obtained in the responder and nonresponder groups will be conducted using the 2-tailed *t* test or Mann-Whitney *U* test for continuous variables and the chi-square test for categorical variables. To determine the independent factors associated with the level of PADL (dependent variable, considering clinical control, smoking, obesity, anxiety, and depression as independent variables), multiple linear regression analysis (stepwise forward) will be used. The intra- and between-group comparison at baseline, short term, and medium term will be assessed using the 2-way ANOVA with repeated measures test. The significance level will be adjusted to 5% (*P*<.05) for all tests. If necessary, intention-to-treat analysis will be performed, as described earlier. SPSS Statistics (version 22.0; IBM Corp) will be used for statistical analysis. Data integrity will be monitored by regularly scrutinizing data files for omissions and errors. Participants will be given an anonymous study ID to protect confidentiality, and only study investigators will have access to the final trial data set.

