### Strengths and Limitations of the Study

In addition to the potential to identify the characteristics of responders and nonresponders, this study will also follow up 4 months after training, considered the medium term. These results will allow us to determine if behavioral changes are maintained in the responders over time. The assessment of PADL using accelerometers as a primary outcome is a study strength because it is an objective outcome measure, thus decreasing the risk of bias. The fact that the study will be performed in only 1 hospital center can be considered a limitation.

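### With no control arm and no date term in the stated analysis, a seasonal change in steps cannot be told apart from kept or lost gains at the medium-term visit, 24 weeks after baseline

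*Protocol article*

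**What the plan says.** All references are to the protocol article.

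- **Visits.** Study Design: "All individuals will be assessed before and after the 8-week intervention and then 16 weeks later". Strengths and Limitations of the Study fixes the anchor of the last visit: "this study will also follow up 4 months after training, considered the medium term". The 16 weeks thus run from the end of the programme, not from baseline.
- **No comparison group.** Abstract, Methods: "All individuals will receive an educational program and an 8-week intervention to increase PADL".
- **Response.** Statistical Analysis Planning separates responders from nonresponders "based on an increase of ≥2500 steps". The rule names no visit.
- **Longitudinal analysis.** Same section: "The intra- and between-group comparison at baseline, short term, and medium term will be assessed using the 2-way ANOVA with repeated measures test".
- **Regression.** The candidate factors for activity level are listed: "considering clinical control, smoking, obesity, anxiety, and depression as independent variables". Neither season nor date of entry is among them.
- **Enrolment period.** Participant Timeline: "The recruitment of the study participants began in May 2022". The Results section describes recruitment as still open, and the article appeared on 31 August 2023.
- **Use of the last visit.** The Discussion says the results will show whether responders keep their behavioural change and whether short-term gains persist. The only limitation it names is the single centre.

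**The concern.** In a single-arm study every change from baseline combines the effect of the programme with whatever else changed over the same weeks. Season is a natural candidate for free-living step counts, and 24 weeks is nearly the longest separation in season that two visits can have (26 weeks being opposite). A concurrent control group would remove a calendar effect, and a date term would estimate it. The stated analysis has neither.

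The medium-term objective is at stake. A patient whose last visit falls in a less active season appears to have lost the gain, and one measured in a more active season appears to have kept it. If more patients enter in one part of the year, the same error carries into the group means on which the conclusion about maintenance rests.

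**Working it through.** **Inputs from the protocol article.** Gaps of 8 weeks (baseline to end of programme), 16 weeks (end of programme to last visit) and 8 + 16 = 24 weeks (baseline to last visit). 24/52 = 0.46 of a year. Threshold 2500 steps, SD 2500, expected nonresponse 17%, N = 100 (Sample Size Calculation).

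**Check of the plan's own figures.** For a difference of 2500 with SD 2500, two-sided 5% and 80% power, the t-based sample size is 16.7, so 17 per group, and 17/0.17 = 100. The stated sample size reproduces and does not depend on this point.

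**Assumption, not in the documents.** Steps follow a yearly cosine with amplitude A (half of peak to trough), A = 300 to 700 steps/day.

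**Largest shift for one patient.** Over a gap of w weeks it is 2A·sin(πw/52).

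| Change | sin(πw/52) | A = 300 | A = 500 | A = 700 |
|---|---|---|---|---|
| Baseline to week 8 (w = 8) | 0.465 | 279 | 465 | 651 |
| Week 8 to week 24 (w = 16) | 0.823 | 494 | 823 | 1152 |
| Baseline to week 24 (w = 24) | 0.993 | 596 | 993 | 1390 |

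The 24-week gap picks up 99% of the full peak-to-trough range 2A; the 8-week gap picks up 46%.

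**Mean shift.** The shift is itself a cosine in the date of entry, so it averages to zero when entry is even over the year. Now let the density of entry dates be 1 + c·cos(2π(d − φ)), with d the date as a fraction of a year. The mean shift is then at most (c/2) × the largest individual shift, reached when the busy season lines up with the shift. Take c = 0.4 as an illustration. The busiest quarter then holds 0.25 + (0.4/π)·sin(π/4) = 34% of patients and the quietest 16%.

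- Baseline to week 24: 0.2 × 596 = 119 to 0.2 × 1390 = 278 steps.
- Week 8 to week 24: 0.2 × 494 = 99 to 0.2 × 1152 = 230 steps.

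If the SD of change were 2500 (the article does not say that its SD refers to change), the standard error of a mean change in 100 patients would be 2500/√100 = 250 steps. The 24-week bias would be about 0.5 to 1.1 standard errors.

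**Responder label at week 8.** With SD of change 2500 and 17% nonresponse, the implied mean change is 2500 + 0.954 × 2500 = 4885 steps. Moving that mean by ±279 (A = 300) gives nonresponse of 14.3% to 20.0% by date of entry; ±651 (A = 700) gives 11.2% to 24.4%.

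**Baseline ACQ and response.** Suppose ACQ also had a seasonal amplitude of 0.1-0.3 points with SD 0.8 (assumptions) and were worst when steps are lowest. A patient who enters at that trough gains A(1 − cos(16π/52)) = 0.43A by week 8, that is 130-302 steps, less than half the maximum in the table. The false correlation between baseline ACQ and the 8-week change is 0.003-0.022, and the false difference in ACQ between responders and nonresponders is 0.005-0.032 points. Even with the two cycles aligned in the worst way and A raised to 1000, the figures are at most 0.07 and 0.10 points. The article treats 0.5 points as clinically significant.

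**The case against.** **The existence of a seasonal effect is assumed, not only its size.** This stands. The Introduction says of asthma symptoms only that they are ones "which can vary over time and in intensity, together with variable expiratory airflow limitation"; it mentions neither season nor steps. Every figure above that depends on A is conditional.

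**Enrolment over more than a year helps.** This also stands in part. May 2022 to August 2023 covers all seasons, and with even entry the mean shift is zero at both visits, so season only adds noise. But a period longer than a year does not make entry even, and the article neither plans for nor describes the distribution of entry dates.

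**A full analysis plan, not shown, could hold a date covariate.** It could, so the absence of a sensitivity analysis from a condensed article counts for little by itself. The point rests on what the article does state: a named ANOVA, a named list of factors without date, and a conclusion about maintenance to be drawn from them.

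**A stronger reading is tempting.** A reader might infer that the half-year gap also distorts the responder label and, through baseline asthma control, creates a false responder characteristic. The documents do not support this. The Abstract gives the responder rule directly after the pre- and postintervention assessments, and the Discussion asks whether changes last in those already classed as responders. Both point to the 8-week change, where the shift is less than half as large. The route through ACQ is too small to matter under the assumptions above. The label would carry the larger exposure only if it were set at week 24, which the rule does not strictly exclude because it names no visit.

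**Conclusion.** The point holds for the medium-term objective. The last visit is 24 weeks after baseline, there is no control arm, and the stated repeated-measures ANOVA cannot separate a seasonal change from kept or lost gains. Under an assumed amplitude of 300-700 steps/day, individual shifts reach 596-1390 steps from baseline and 494-1152 steps from week 8. The group mean is nearly unaffected by even entry. With 34% of patients in the busiest quarter it could be off by about 119-278 steps from baseline.

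For the first objective, finding who responds, season is a minor source of noise in the 8-week label and not a demonstrated source of false characteristics. The sample size is unaffected. The point calls for a cheap sensitivity analysis, not a change of design.

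**What to change.** Add a sensitivity analysis to Statistical Analysis Planning:

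1. Re-estimate the week-24 change in steps and in ACQ, once from baseline and once from week 8, with one sine and one cosine term of enrolment date (52-week period). With fixed gaps between visits, these two terms capture any yearly cosine in the outcome.
2. Report the season-averaged change beside the ANOVA result.
3. Show the number enrolled and the responder share by quarter of enrolment.
4. Qualify any statement that gains were maintained or lost if it changes under the adjustment.
5. State in the responder rule which visit it uses.

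**Cost.** Only analysis wording changes, provided visit dates are kept. The model spends two degrees of freedom among about 100 patients. Even entry costs almost no precision. With the uneven pattern above (c = 0.4), the standard error of the season-averaged change grows by a factor √(1 + 0.2²/(0.5 − 0.2²)) = 1.04. Strong clustering in one season would widen intervals more, which would show that the data cannot separate season from maintenance.

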**Figure 1 figure1:**
[figure not shown]
Study design. PADL: physical activity in daily life.

### Participants

The study will include both male and female adults aged 18 to 65 years with moderate to severe asthma [1] who are not physically active (<150 min of moderate to vigorous physical activity/wk [15] or ≤7500 steps/d) and have partially controlled or uncontrolled asthma (Asthma Control Questionnaire [ACQ] score ≥0.75) [16]. In addition, the following inclusion criteria will be considered: diagnosis of asthma based on the recommendations established by GINA [1], outpatient medical treatment for at least six months, and a stable clinical status for at least 30 days (no hospitalizations, visits to emergency services, or medication changes) [17]. Pharmacotherapy will be maintained throughout the intervention period. After being informed about the possible risks and benefits of the study, participants will be instructed to sign an informed consent form.

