**Assessments:**						
	Lung function			✓		
	PADL^a^ and sedentary behavior	✓			✓	✓
	Asthma Control	✓			✓	✓
	Asthma exacerbations			✓	✓	✓
	Quality of life			✓	✓	✓
	Anxiety and depression			✓	✓	✓
	Barriers to perform PADL			✓	✓	✓
	Behavioral stage for PADL			✓	✓	✓
	Anthropometric data			✓	✓	✓
	Body composition			✓	✓	✓

^a^PADL: physical activity in daily life.

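### For steps and ACQ the screening reading is also the baseline, so in a single-arm study regression to the mean adds modestly to apparent response

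*Protocol article*

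**What the plan says.** - **Entry (Participants).** Patients must be inactive, defined as "<150 min of moderate to vigorous physical activity/wk [15] or ≤7500 steps/d", where either limb is enough, and must "have partially controlled or uncontrolled asthma (Asthma Control Questionnaire [ACQ] score ≥0.75".
- **Timing (Table 2, Assessments).** The rows "PADL^a^ and sedentary behavior" and "Asthma Control" are ticked at Enrollment, 8 weeks and 16-week follow-up, and their Baseline cell is empty. The row "Quality of life" is ticked at Baseline and not at Enrollment. So are exacerbations, anxiety and depression, barriers, behavioral stage, anthropometry and body composition.
- **Arms (Abstract, Methods).** "All individuals will receive an educational program and an 8-week intervention to increase PADL". There is no comparison group.
- **Use of the change (Statistical Analysis Planning; Sample Size Calculation).** A responder is a patient whose steps rise by at least 2500. An ACQ improvement of at least 0.5 is a secondary outcome. Change from baseline to short and medium term is tested by repeated-measures ANOVA.
- **Interpretation.** The second objective is to "evaluate the functional and clinical benefits in the medium term". The Abstract's conclusion is that identifying responders "will help clinicians prescribe specific interventions to adults with asthma". The Strengths and Limitations section names only the single centre as a limitation.

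**The concern.** A patient admitted on a low activity reading or a high ACQ reading will on average move back towards their usual level at the next reading, even if nothing has changed. A separate baseline reading after admission would remove this effect. Table 2 provides one for every repeated outcome except the two that decide entry. A control arm would let the effect be subtracted, and there is none.

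Three results are exposed: mean change in steps and ACQ, the share labelled responders, and any association between response and baseline steps or baseline ACQ. The third matters because asthma control is one of the characteristics that the Introduction expects to predict response. Baseline steps are not among the independent variables listed for the regression.

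**Working it through.** **1. The plan's own figures.** Two-sample t test, difference 2500, SD 2500, two-sided 5%, power 80%: 16.71 per group, rounded up to 17; 17/0.17 = 100. Both reproduce and are not in dispute.

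**2. Model.** Screening reading X0 = T + e0 and later reading X1 = T + e1, with the same true level T (no true change) and independent errors. Reliability R is var(T)/var(X). Then

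E[X1 − X0 | admitted] = (1 − R) × (μ − E[X0 | admitted]).

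From the protocol: the 7500-step and 150-minute cuts, the 2500-step and 0.5-point thresholds, and SD 2500 (a planning figure, borrowed here as the between-patient SD). Assumed: source mean μ 6000–9000, SD 2500–3500, R 0.6–0.9. For the either/or rule, also assumed: a correlation of 0.7 between MVPA and the same week's steps, and half of the source population below the MVPA cut.

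**3. Mid-range case: μ = 7500, SD 2500, R = 0.8.**
- Cut on steps alone: μ − E[X0 | X0 ≤ 7500] = 2500 × √(2/π) = 1995. Shift = 0.2 × 1995 = 399 (simulation 402).
- Either/or rule: admitted fraction = 1 − [1/4 + arcsin(0.7)/(2π)] = 0.627. Mean deficit of those admitted = 0.3989 × 0.5 × (1 + 0.7)/0.627 = 0.541 SD = 1353 steps. Shift = 0.2 × 1353 = 271 (simulation 271).

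**4. Share crossing 2500 from noise alone, with a fresh baseline.** 1 − Φ(2500/(√2 × 2500 × √(1 − R))) = 1.3%, 5.7%, 9.8% and 13.2% for R = 0.9, 0.8, 0.7 and 0.6. Reuse of the screening reading does not cause this part.

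**5. Steps, either/or rule, no true change (simulation, 1,000,000 patients per scenario).**

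| μ / SD / R | Mean change, screening value as baseline | ≥2500, screening value | ≥2500, fresh baseline | Added by reuse |
|---|---|---|---|---|
| 6000 / 2500 / 0.9 | +95 | 1.5% | 1.3% | 0.2 per 100 |
| 7500 / 2500 / 0.8 | +271 | 7.5% | 5.7% | 1.8 per 100 |
| 7500 / 2500 / 0.6 | +543 | 18.0% | 13.2% | 4.8 per 100 |
| 9000 / 3500 / 0.6 | +815 | 28.8% | 21.2% | 7.6 per 100 |

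The first and last rows are the extremes of the grid. With a fresh baseline the mean change is about 0 in every scenario.

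**6. ACQ, cut at ≥0.75 (assumed mean 1.0–2.0, SD 0.8–1.0, R 0.7–0.9).** Mean change is −0.01 to −0.20 points, where lower is better. The share improving by ≥0.5 is 8% to 34% from the screening value and 8% to 26% from a fresh baseline. At mean 1.5, SD 0.8, R 0.8 the mean shift is −0.05, with 18.2% against 16.2% improving.

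**The case against.** **The schedule might hide a separate baseline.** Study Design and Outcome Measures promise assessment before the intervention, and a table read from PDF can shift. But exactly the two entry variables sit under Enrollment, and every other repeated outcome sits under Baseline. That pattern looks deliberate. If a separate reading was in fact taken, Table 2 should be corrected and the reuse point falls away.

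**The activity rule is either/or.** This stands. A reader might treat it as a cut on steps alone, which gives up to 1527 steps/d over the same assumed ranges. Patients above 7500 steps can enter on MVPA, so that is not the protocol's rule.

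**Noise and selection are different things.** This stands too. A reader might attribute every false responder to the reused screening value. Most would cross 2500 with a fresh baseline as well.

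**Most outcomes are untouched.** Correct. Quality of life, HADS, barriers, exacerbations and body composition are ticked at Baseline and are not entry thresholds. The comparison of 8 weeks with the 16-week follow-up does not use the screening value. A reader might infer that the whole responder profile is distorted. Step error unrelated to age, obesity or HADS mainly dilutes those contrasts; the clear distortion concerns baseline steps, baseline ACQ and their correlates.

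**Adjustment belongs in an analysis plan that is not shown.** Partly fair. The measurement schedule and the wording of objective and conclusion are in the protocol, however, and its limitations do not mention the reuse.

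**Conclusion.** The point holds in a limited form. Under Table 2, the only steps and ACQ values before the intervention are the ones that admitted the patient, and with one arm the resulting bias always runs towards response. Under the either/or rule and no true change it is about +95 to +815 steps/d. Reuse adds about 2 responders per 100 in the mid-range case and about 0.2 to 7.6 across the grid. The mean ACQ shift of 0.01 to 0.20 points has the same direction but stays below the 0.5-point threshold.

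These sizes depend on source means, SDs, reliabilities and an MVPA–steps correlation that are assumptions. The documents do not support the reading that regression to the mean explains most ≥2500-step responses: at reliability 0.9 the whole no-change responder share under the either/or rule, noise included, is 1.5% to 6.9%. Nor do they support extending the point to the outcomes first measured at Baseline. The sample-size arithmetic is unaffected.

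**What to change.** 1. Include baseline steps as a covariate in the responder versus nonresponder comparisons, for example by logistic regression of responder status on one characteristic at a time plus baseline steps (only about 17 nonresponders are expected). State that associations of baseline steps or baseline ACQ with response are partly regression to the mean. The covariate does not repair individual responder labels.
2. Beside the observed responder share, report the share expected with no true change over a stated range of reliabilities. Reliability estimated from days within one week misses variation between weeks and seasons, so treat it as an upper bound.
3. For steps and ACQ, word the conclusions as change over time in an uncontrolled cohort and as factors associated with a step increase. Add reuse of the screening value to the limitations.
4. Report a mean change corrected for regression to the mean only as a sensitivity analysis, and only if accelerometry from screened-out patients is available. The formula needs the source mean, which admitted patients alone do not supply.

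The cost is a small extra calculation and a more modest claim. No new visit, device week or arm is needed, so the change is feasible with recruitment under way.
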